**Figure 3 F3:**
[figure not shown]
Illustration of the confidence interval approach to interpret results from randomised trials. The horizontal line indicates the difference between CRQ change scores between study groups. ± 0.5 points represent the predefined boundaries of equivalence. If the whole confidence interval is on the right of 0.5 points, interval exercise is not inferior to continuous exercise. If the whole confidence interval is within boundaries the two exercise protocols are of clinically equivalent effectiveness (upper three confidence intervals). Note that there can be a statistically significant difference between study groups but without any clinical relevance.

Most methodologists and statisticians agree that the boundaries of equivalence should be defined as the minimal important difference and below the differences observed in previous trials comparing active to control treatments.[13,39] The minimal important difference is "the smallest difference in score in the outcome of interest that informed patients perceive as important, either beneficial or harmful, and which would lead the clinician to consider a change in the management"[40]. Therefore, the minimal important difference of our two main outcome measures for effectiveness have been established empirically and are around 0.5 for the CRQ domains scores [41-44] and 53 meters for the six-minute walk test[45]. A recent meta-analysis showed that respiratory rehabilitation with physical exercise leads to improvements of 50 meters in the six-minute walk test. Therefore we lower the boundaries for equivalence to ± 45 meters in order to have boundaries that are below the differences observed in previous trials comparing active to control treatments.[13,39]

We will repeat the analysis with calculations of raw and adjusted differences for all other clinical and physiologic outcome measures and test for significant differences between groups using independent t-test if data are distributed normally.

We will use both intention to treat and per protocol analysis to show equivalence in either case as recommended by others[13,39,46,47]

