### Effectiveness

Our null hypothesis is that high intensity continuous exercise is of clinically superior effectiveness compared with interval exercise to improve HRQL (δ ≥ 0.5 in CRQ domains scores). The alternative hypothesis is that interval exercise is not of clinically inferior effectiveness compared with high intensity continuous exercise.

In the primary analysis, we will calculate the raw difference and 95% confidence intervals between groups in the mean follow-up score for the CRQ domains 2 weeks after completion of the respiratory rehabilitation programme. In an additional analysis, we will adjust for the base-line score and the four stratification variables using an analysis of covariance. We will use independent t-test to compare the change scores between groups.

We will also use the confidence interval approach as recommended for equivalence and non-inferiority trials[13] We will establish non-inferiority of interval exercise if the point estimate and its 95% confidence interval for difference between the change scores of the continuous and interval exercise group is smaller than the a priori determined boundary of clinical equivalence (see figure 3). If the 95% confidence intervals lie outside the boundaries of clinical equivalence we will establish clinical superiority of one exercise protocol.

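### The Figure 3 legend puts the non-inferiority threshold at the wrong boundary, and its direction conflicts with the rule in the Effectiveness text

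*Protocol article*

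**What the plan says.** The Effectiveness section of the protocol article states this null hypothesis: "high intensity continuous exercise is of clinically superior effectiveness compared with interval exercise to improve HRQL (δ ≥ 0.5 in CRQ domains scores"). Against it stands the alternative that interval exercise is not clinically inferior.

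The same section gives the decision rule and refers the reader to Figure 3. Non-inferiority is declared on this condition, which applies to the point estimate as well: "95% confidence interval for difference between the change scores of the continuous and interval exercise group is smaller than the a priori determined boundary". The boundary meant is the edge of the equivalence zone. A separate outcome is reserved for results beyond the boundaries: "If the 95% confidence intervals lie outside the boundaries of clinical equivalence we will establish clinical superiority of one exercise protocol".

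The legend to Figure 3 describes the axis in these words: "The horizontal line indicates the difference between CRQ change scores between study groups". It places the boundaries at ±0.5 and gives two rules:

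- Non-inferiority: "If the whole confidence interval is on the right of 0.5 points, interval exercise is not inferior to continuous exercise".
- Equivalence: "If the whole confidence interval is within boundaries the two exercise protocols are of clinically equivalent effectiveness".

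Neither the text nor the legend says which group is subtracted from which.

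**The concern.** With a zone of −0.5 to +0.5, non-inferiority is a one-sided question: does the confidence interval exclude the boundary that is unfavourable to interval exercise? The legend asks instead whether the whole confidence interval lies beyond +0.5. That is a different question whichever way the difference is taken.

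The text and the legend also point in opposite directions. A confidence interval below the boundary is good news for interval exercise only if the difference is continuous minus interval. A confidence interval to the right is good news only if it is interval minus continuous.

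Non-inferiority is the trial's primary objective, and this is the only rule in the article that can decide it. The Data analysis section adds to the need for clarity. Investigators see only group codes, and two manuscripts are drafted before the code is broken. A one-sided conclusion drafted under coded groups needs a direction and a threshold that can be read in one way only.

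**Working it through.** **Inputs.** From Sample size: 44 evaluable patients per group, SD 0.8 (range given 0.8 to 1.2), difference 0.5, power 90%, one-sided 5%, drop-out 15%. From Effectiveness and the Figure 3 legend: boundaries ±0.5 and a 95% confidence interval. Normal approximation throughout.

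**The plan's own figure.** n = (1.645 + 1.282)² × 2 × 0.8² / 0.5² = 43.85, so 44 per group. 44 / 0.85 = 51.8, so 52 per group and 104 in total. This reproduces. The same 44 follows for a non-inferiority margin of 0.5 with a true difference of 0, so the trial was not sized for the legend's sentence.

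**Reading the legend's sentence under each direction.**

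| Direction of difference | Meaning of a CI wholly above +0.5 | Label in Effectiveness text | Label in legend |
|---|---|---|---|
| Interval minus continuous | interval better by more than 0.5 | clinical superiority (of interval) | not inferior |
| Continuous minus interval | continuous better by more than 0.5 | the null region; clinical superiority (of continuous) | not inferior |

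In the first row the legend's label is true but is attached to the wrong threshold. In the second row it is false.

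**Size, SD 0.8.**

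- SE = 0.8 × √(2/44) = 0.1706. Half-width of the 95% CI = 1.96 × 0.1706 = 0.334.
- Legend's non-inferiority sentence: the estimate must exceed 0.5 + 0.334 = 0.834. With equal arms, P(Z > 0.834/0.1706 = 4.89) ≈ 5 × 10⁻⁷. On an interval-minus-continuous axis, 90% probability needs a true advantage of 0.5 + (1.96 + 1.282) × 0.1706 = 1.05 points. On a continuous-minus-interval axis, the sentence is met with probability 83.4% when interval exercise is truly worse by 1.0 point.
- Rule in the text (lower limit of interval minus continuous above −0.5, or equivalently upper limit of continuous minus interval below +0.5): with equal arms, Φ(0.5/0.1706 − 1.96) = Φ(0.97) = 83.4%. At the null boundary it is 2.5%.
- Legend's equivalence rule with equal arms: 2 × 0.8344 − 1 = 66.9%.

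**The unlabelled gap (interval minus continuous).** A CI above −0.5 that crosses +0.5 is non-inferior by the text but has no label in the legend. With equal arms its probability is 83.4% − 66.9% = 16.6% before rounding (0.8344 − 0.6687 = 0.1657). If interval exercise is truly better by 0.25, it is 0.9926 − 0.3032 − 0.0003 = 68.9%.

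**Sensitivity, SD 1.2.** SE = 0.256 and half-width = 0.501. The legend's sentence needs an estimate above 1.00, with probability 4.5 × 10⁻⁵ for equal arms, against 49.8% for the rule in the text. The equivalence rule cannot be met with 44 per group, because the half-width exceeds 0.5.

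**The case against.** Four points can be made for the plan.

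**The legend states a sufficient condition, not a necessary one.** This stands. A reader might infer that the legend allows non-inferiority only beyond +0.5, so that a trial with equal arms could not succeed. The legend does not say that. Its next sentence labels a CI wholly within the boundaries as equivalent, which implies non-inferior, and equal arms would meet that rule about 67% of the time at SD 0.8. The 5 × 10⁻⁷ and the 1.05 points describe the one sentence in isolation.

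**A minus sign may have been lost, in the article or when the text was read from the PDF.** This cannot be excluded, although the ± sign in the preceding sentence survived. A threshold of −0.5 would be correct for interval minus continuous. It would not remove the conflict of direction with the text, which lists continuous first and asks for a CI below the boundary.

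**The figure may show the direction.** This stands too. The figure is not shown, so one cannot say that the direction is stated nowhere. Only its absence from the text and legend can be claimed. For the same reason, a reader might infer that the legend calls interval exercise non-inferior exactly when it is clinically inferior. That holds only if the unseen axis is continuous minus interval. On the other axis, superior and not inferior are compatible labels.

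**The rule in the text is sound, and the CI approach is introduced as an addition to a comparison of follow-up scores.** The text rule is workable and agrees with the null hypothesis and the sample size. But the text cites Figure 3 for that rule, so a wrong threshold there is part of the stated rule.

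**Conclusion.** The point holds. The legend's threshold for non-inferiority is wrong under either direction of subtraction, and the text and legend imply opposite directions. On an interval-minus-continuous axis, the practical effect is a missing label for CIs that lie above −0.5 and cross +0.5: about 17% of trials with equal arms at SD 0.8, and about 69% if interval exercise is truly better by 0.25. On a continuous-minus-interval axis, the legend would attach the non-inferior label to results in the null region.

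These figures assume 44 evaluable patients per group, the protocol's SD, a two-sided 95% CI and the normal approximation. The 83% is below the planned 90% because the sample size uses a one-sided 5% level while the rule uses a 95% CI. That is a separate matter and is not caused by the legend. The documents do not show that the design was built on the legend's threshold; the sample size indicates the opposite.

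**What to change.** State the direction of subtraction once, in the Effectiveness text, and repeat it in the legend and on the axis. One workable choice is interval minus continuous, with positive values favouring interval exercise. Then use one set of rules in both places:

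- Non-inferior: lower 95% limit above −0.5.
- Equivalent: whole CI within −0.5 to +0.5.
- Interval exercise clinically superior: whole CI above +0.5.
- Interval exercise clinically inferior: whole CI below −0.5.
- Otherwise: inconclusive.

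In the legend's non-inferiority sentence, change the threshold from 0.5 to −0.5. In the text, reword the non-inferiority rule so that it follows the chosen direction. The cost is wording only: no patients, no data and no change to the sample size. It should be done before the group code is broken and before the two manuscript versions are drafted.

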### Exercise tolerance

Our null hypothesis is that patients equally experience high intensity continuous exercise and interval exercise as measured by the Exercise Tolerance Questionnaire. The alternative hypothesis is that interval exercise is associated with the experience of less limiting symptoms compared with high intensity continuous exercise.

We will use independent t-tests to compare the measures for exercise tolerance (Exercise Tolerance Questionnaire, Borg scales for dyspnoea and leg pain) between groups. Again, we will assess the raw differences between groups in the primary analysis and adjust for baseline scores and the four stratification variables in the additional analysis.

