#### Group performing continuous exercise

The target workload for this group will be ≥ 70% of the maximum exercise capacity expressed in Watts and heart rate achieved during the incremental cycle ergometer test. Patients are usually not able to perform high intensity continuous exercise from the beginning and have to adapt to physical exercise. Physical therapists will increase training load as soon as possible to ≥ 70% of the maximum exercise capacity or as high as each individual patient tolerates. In each session (see figure 2), patients will have a warm-up period of two minutes at 20% of maximum exercise capacity, increase the exercise intensity within two minutes to the target intensity, exercise for 20 minutes at high intensity and then have a decreasing period of two minutes (gradual decrease from 70% to 0%). Pulse oxymetry will be used to supervise patients during exercise. If oxygen saturation falls below 90%, oxygen supplementation will be provided to maintain ≥ 90%.

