**Figure 2 F2:**
[figure not shown]
The upper graph shows the continuous exercise protocol for a patient who achieved a maximum exercise capacity of 100 Watts during a usual incremental exercise test. The lower graph shows the interval exercise protocol for a patient who achieved a short time muscular exercise capacity of 200 Watts during a steep ramp test.

If patients cannot sustain the workload because of perceived dyspnoea or leg fatigue or because the heart rate exceeds the limits determined during exercise testing, physical therapists will let patients rest for one minute and then resume exercise. If patients have to rest more than twice per session, physical therapists will lower the workload by steps of 10% of baseline maximum exercise capacity. In turn, if patients or physical therapists consider the workload to be too low or if patients do not reach their target heart rate at 70% of the maximum exercise capacity, physical therapists will increase workload by steps of 10% of maximum exercise capacity until patients and physical therapists consider the workload to be appropriate or until the target heart rate is reached.

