If patients cannot sustain exercise intensity because the heart rate exceeds the limits determined after exercise testing or because of perceived dyspnoea or leg fatigue, physical therapists will let patients rest for one minute and then resume exercise. If patients have to rest more than twice per session, physical therapists will lower the workload from 50% of the short time maximum exercise capacity by steps of 10% while the length of intervals remains constant. They will increase the training load again as possible for the patient.

In turn, if patients or physical therapists consider the workload to be too low, physical therapists will increase workload of the high intensity interval by steps of 10% until patients and physical therapists consider the workload to be appropriate while the length of intervals remains constant.

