#### Adherence to and tolerance of the prescribed cycle ergometer exercise

Physical therapists will record for every cycle ergometer exercise session if patients exercised at all (yes or no), the performed workload (in Watts), if patients reached the target workload (in Watts), adjustments of workload and the requirement for oxygen. We define adherence to exercise as "full adherence" if patients follow at least 12 exercise sessions. We consider the training to be fully tolerated if patients are able to follow the exercise protocol for at least 9 exercise sessions for continuous exercise (taking into consideration the first three exercise session when patients increase training load up to 70% of maximum exercise capacity) and for at least 12 exercise sessions for interval exercise.

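### The tolerance comparison uses only symptom scores taken at a workload already adjusted to symptoms, so a real tolerance difference can be partly hidden

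*Protocol article*

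**What the plan says.** Better tolerance of interval exercise is the secondary objective (Protocol article, end of Background).

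**How load is set.** In the continuous arm, load rises to at least 70% of maximum capacity "or as high as each individual patient tolerates" (Group performing continuous exercise). The text after Figure 2 starts the downward rule with "If patients cannot sustain the workload because of perceived dyspnoea or leg fatigue", or with an exceeded heart-rate limit. The patient then rests for a minute, and if more than two rests are needed in a session, "physical therapists will lower the workload by steps of 10% of baseline maximum exercise capacity". Load goes up if it is thought too low or if the target heart rate is not reached. The interval arm has a parallel downward rule. Upward, "physical therapists will increase workload of the high intensity interval by steps of 10% until patients and physical therapists consider the workload to be appropriate" (Group performing interval exercise).

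**When symptoms are rated.** Borg scores for dyspnoea and leg pain are taken five minutes into each session and at its end. The Exercise Tolerance Questionnaire asks how patients experienced the sessions (both under Monitoring of exercise sessions).

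**What is tested.** The hypothesis is set on the questionnaire: "Our null hypothesis is that patients equally experience high intensity continuous exercise and interval exercise as measured by the Exercise Tolerance Questionnaire". The test is: "We will use independent t-tests to compare the measures for exercise tolerance (Exercise Tolerance Questionnaire, Borg scales for dyspnoea and leg pain) between groups". A further analysis will "adjust for baseline scores and the four stratification variables in the additional analysis".

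**What else is recorded.** For every session therapists note attendance, performed workload and "if patients reached the target workload (in Watts), adjustments of workload and the requirement for oxygen". The same section calls training fully tolerated when the exercise protocol is followed for at least 9 sessions (continuous) or at least 12 (interval).

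**The concern.** When symptoms help to determine load, load and symptoms are two halves of one response. A patient who finds the prescribed work too hard can express this as a high score at the prescribed load or as a lower load with a moderate score. The titration rules move patients from the first form to the second. A comparison that looks only at scores then sees what the titration has left over.

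The protocol itself expects this to matter more in one arm. The Background says that fewer than 20% of such patients may sustain high intensity continuous exercise throughout a programme, and the continuous-exercise section says patients usually cannot manage it at the start. At stake is the second half of the trial's rationale. The Background says interval exercise will be accepted only if it is not inferior and is also associated with better compliance through fewer symptoms. A score comparison pulled towards zero could leave that claim unsupported even though the load record shows a difference.

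**Working it through.** **1. The plan's own figure.** The protocol gives no sample size or power for tolerance, only for the CRQ. With one-sided 5%, 90% power, SD 0.8 and difference 0.5: n = (1.645 + 1.282)² × 2 × 0.8² / 0.5² = 43.9, so 44 per group. Then 44 / 0.85 = 51.8, so 52 per group and 104 in total. Both stated figures reproduce. They are unaffected by this point and are used below only for n = 44.

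**2. Sections side by side.**

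| Element | Depends on symptoms? | In the tolerance tests? |
|---|---|---|
| Workload, both arms | Yes, in part | No |
| Borg scores | Rated at the adjusted load | Yes |
| Exercise Tolerance Questionnaire | Answered about sessions at the adjusted load | Yes |
| Target attainment and adjustments | Yes | No |
| Full-tolerance criterion | Yes | No |

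The adjusted analysis adds baseline scores and the stratification variables, not load. The general provision in the Effectiveness section repeats the analysis for other clinical and physiologic outcome measures. Workload and adherence are described under Monitoring of exercise sessions, so it does not clearly reach them.

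**3. Is the existing criterion like for like?**
- Patient attending 12 sessions: the continuous arm may fall short in 12 − 9 = 3, the interval arm in 12 − 12 = 0.
- Patient attending 15 sessions: 15 − 9 = 6 against 15 − 12 = 3.

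The protocol explains the 9 by three build-up sessions in the continuous arm. Even so, the interval arm must succeed in three more sessions to be counted as tolerant. It is also unclear whether a patient stepped down under the protocol's own rule still counts as following the protocol.

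**4. What a step-down does to load (illustration only).** For the 100 W maximum used in Figure 2, the continuous target is 0.70 × 100 = 70 W. One 10% step gives 60 W (60/70 = 86% of target) and two give 50 W (50/70 = 71%). The score tests would treat ratings at 70 W and at 50 W alike.

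**5. Can masking occur? (simulation on assumed inputs).** The assumptions, none of them from the protocol except that 44 is its per-group n and 12 its minimum number of sessions, are:
- 44 per arm, 12 sessions, and a true gap of 1.0 Borg point at equal load;
- between-patient SD 1.5 and session SD 0.7;
- 0.7 Borg points per 10% of target load;
- load lowered one step if Borg exceeds 5 and raised one step if below 3;
- two-sided 5% t-test on patient means, 2,000 runs.

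Titration shrinks the mean score gap from about 1.0 to about 0.27, so about 73% of it disappears, while an achieved-load gap of about 10% of target opens up. Power depends on how much patient-level reporting variation sits in the scores without driving the load:

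| Extra reporting SD | Score test, no titration | Score test, titration | Test on achieved load |
|---|---|---|---|
| 0 | 86.3% | 80.5% | 84.3% |
| 0.5 | 83.5% | 48.1% | 85.5% |
| 1.0 | 71.4% | 20.7% | 85.8% |
| 1.5 | 58.5% | 12.1% | 85.3% |

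In the first row titration also compresses the spread of scores, so little power is lost. This shows that masking can happen. It does not estimate how much would occur in this trial.

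**The case against.** The other side has a good deal on its side.

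- **Tolerance is not conceived only as symptoms.** The monitoring section has a protocol-based criterion and a session-by-session load record. This stands, and it makes the remedy cheap.
- **This is detail for an analysis plan.** A yes/no criterion would not be listed among t-tests, so its absence from that list does not prove it will go uncompared. True, but the article itself fixes the hypothesis and names the tolerance measures, and the criterion it defines has unequal thresholds. That is more than missing detail.
- **Titration is limited.** A reduction needs more than two rests in one session, the continuous arm keeps its 70% target, and a target heart rate also pushes its load upward. A Borg score is taken as early as five minutes, and the questionnaire asks about too high a load. These points stand: masking is partial. The simulated rule acts directly on the Borg score and is tighter than the protocol's.
- **Experience under training as delivered is a legitimate pragmatic question.** Agreed. It is still incomplete as evidence on tolerance if the load at which it was experienced is left out.

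Three stronger readings are tempting, and the document does not support them. First, a reader might infer that about 42 of 52 continuous patients (80% of 52 = 41.6) would be stepped down. The 20% figure is a cautious statement about sustaining high intensity throughout a programme, which is not the same as a reduction under the rest rule, so 42 is at most an upper bound. Second, one might infer that the investigators would read non-significance as equal tolerance. Their Background rejects that inference for effectiveness in earlier trials. Third, one might infer that rests go unrecorded. They are not in the listed items, but the data forms are not shown and may capture them.

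**Conclusion.** The point holds in a limited form. Load is adjusted partly to symptoms in both arms, the named tolerance measures are rated at the adjusted load, and the stated tests take no account of load. Followed as written, the analysis can understate a real tolerance difference on the secondary objective. Its size cannot be derived from the document: under the assumed inputs the loss of power runs from slight (86.3% to 80.5%) to severe (58.5% to 12.1%), depending on reporting variation that the protocol does not give. The load-based criterion that would complement the scores exists but is not tested, and its thresholds of 9 and 12 sessions do not compare like with like. The primary CRQ analysis and the sample size are not affected.

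**What to change.** Change the Exercise tolerance section as follows and leave the titration rules as they are.

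1. Add a between-arm comparison of protocol-based tolerance from the existing records: the proportion of sessions completed at the protocol target without a workload reduction, counted over the same sessions in both arms. One window that respects the protocol's own reasoning is sessions 4 to 12 (nine sessions) in each arm. State how missed sessions count, and that a stepped-down session is not a session at target.
2. Report Borg and questionnaire scores beside achieved workload as a percentage of target, by arm. Since the two targets come from different exercise tests, note that this percentage measures attainment of each prescription, not equal work.
3. State in advance that similar symptom scores with lower achieved load in one arm will not be read as equal tolerance.

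The cost is one additional secondary comparison. The workload, target and adjustment data are already collected at every session.
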